### 5.4.2 Secondary study parameters/endpoints

Economic perspectives (such as costs) of the care pathway will be evaluated.

## 5.5 STATISTICAL ANALYSIS

Primary and secondary study parameters and endpoints are described in 'Study parameters/endpoints'. All statistical analyses will be performed with SPSS 24.0 for Windows (IBS, SPSS Statistics, Chicago, IL, USA). Descriptive statistics will be used for frequencies, percentages, means and standard deviations. Continuous variables will be analysed using independent t-tests, whereas the categorical data will be analysed by chi-square or Fisher's exact test. Median and interquartile ranges of non-normally distributed categorical and metric variables of the study will be

assessed using Mann-Whitey-U-test. Prevalence of the most frequent diagnosis (coded ICD-10) at discharge will be presented in percentages. HR and corresponding 95% confidence intervals will be calculated. Generalized Estimating Equations (GEEs) will be used, which adjust for observations made within the same hospitals being more alike. All tests will be performed using a significance level of  $\alpha = 0.05$ . A two-sided p-value  $< 0.05$  will be considered significant.

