### 5.1.5 Sample size

We hypothesize that implementing the care pathway will reduce the mean ED-LOS with 10%. In a prospective study about the quality of Acute Care, by [name] (submitted for publication), the mean length of stay at the ED in the Maxima Medical Centre is three hours and twenty minutes (95% CI 3:00-3:40, SD=1.17). Assuming a normal distribution, a two sided test, power of 80% and a significance level ( $\alpha$ ) of 0.05, a minimum of 466 patients need to be included, 233 patients in both control and intervention group. We aim to include 300 patients in each group, with a estimated timeframe of one year. Each hospital will gather their own control-group before implementation of the care-pathway. A minimum number of control-patients will be established for each participating hospital, dependent of number of annual patient-visits at the Emergency Department.

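### The hypothesis and sample size concern mean ED-LOS, but an undefined normality judgement can move this primary outcome to a rank test that does not address the mean

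*Protocol*

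**What the plan says.** ED-LOS is one of the two primary objectives (Protocol section 3) and is measured in hours (section 5.4.1).

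Section 5.1.5 frames the question as a change in the mean: "We hypothesize that implementing the care pathway will reduce the mean ED-LOS with 10" per cent. The planning values are a control mean and spread of "three hours and twenty minutes (95% CI 3:00-3:40, SD=1.17". The calculation is made "Assuming a normal distribution, a two sided test, power of 80% and a significance level" of 0.05, and the result is "a minimum of 466 patients need to be included, 233 patients in both control and intervention group". The recruitment target is 300 per group.

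Section 5.5 then gives general rules by type of variable:

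- "Continuous variables will be analysed using independent t-tests".
- Non-normally distributed metric variables, summarised by median and interquartile range, are to be "assessed using Mann-Whitey-U-test".
- GEE will be used to allow for similarity of patients within a hospital. No outcome, link function or precedence over the simple tests is stated.

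The section does not say how non-normality will be judged, and it does not name the test for ED-LOS.

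**The concern.** The section states a rule, and one branch of it does not answer the question in section 5.1.5. Mann-Whitney compares rank order between groups. It yields neither a difference nor a ratio of means, so nothing it reports can be set against a 10% fall in the mean. As a two-group test it also takes no account of hospital, although section 5.5 itself recognises that patients within a hospital are alike.

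The choice between branches is made after the data are seen, by an unstated criterion. With GEE also listed, there are three candidate analyses of ED-LOS, and the text does not say which decides. If they disagree, the conclusion on a primary endpoint depends on a choice made after the results are known.

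**Working it through.** **1. Does the stated sample size refer to means?**

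Inputs from section 5.1.5: control mean 3 h 20 min = 200 min; fall of 10% = 20 min; two-sided alpha 0.05; power 80%. The SD is printed as 1.17 without a unit.

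Formula: n per group = 2 × (1.960 + 0.842)² × SD² / difference² = 15.70 × (SD / 20)².

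- SD read as 1 h 17 min = 77 min: 15.70 × (3.85)² = 15.70 × 14.82 = 232.7, so 233 per group and 466 in total. This is the protocol's figure.
- SD read as 1.17 h = 70.2 min: 15.70 × (3.51)² = 15.70 × 12.32 = 193.4, so 194 per group and 388 in total. This does not match.

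The stated size is therefore a two-sample comparison of means with an SD of 77 min, and that reading is used below.

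**2. Could the rank branch be taken?**

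The protocol gives no shape for ED-LOS. Assume log-normal with mean 200 and SD 77. The coefficient of variation is 77/200 = 0.385, and the skewness is 3 × 0.385 + 0.385³ = 1.21. In samples of 233 and of 300 drawn from this distribution, a Shapiro-Wilk test rejected normality in 100% of cases. With a gamma shape it did so in about 99%. Both the shape and the normality test are assumptions, since section 5.5 names neither.

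**3. Why the mean and the ranks can part company**

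Under that log-normal the control median is 200 / √(1 + 0.385²) = 200 / 1.0715 = 186.6 min. If the pathway shortened only the time spent beyond 200 min, enough to lower the mean by 20 min, the median would stay at 186.6 min. The hypothesised fall would be fully present with no change in the median.

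**4. Power at 233 per group**

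The mean falls by 20 min in every row. Patients are independent, tests are two-sided at 5%, and the t-test is Welch's. With 4,000 replicates the simulation error is at most about 1.96 × √(0.25/4,000) = 0.015.

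| Shape of the effect | t-test | Mann-Whitney |
|---|---|---|
| Normal stays, uniform shift | 0.79 | 0.77 |
| Log-normal, uniform shift | 0.80 | 0.88 |
| Log-normal, every stay × 0.9 | 0.84 | 0.85 |
| Gamma, uniform shift | 0.79 | 0.81 |
| Gamma, every stay × 0.9 | 0.84 | 0.81 |
| Log-normal, benefit in a random 20-50% of patients | 0.78-0.82 | 0.86-0.88 |
| Log-normal, fixed time off the longest 50% of stays | 0.87 | 0.84 |
| Log-normal, fixed time off the longest 33% to 10% | 0.89-0.92 | 0.60-0.72 |
| Log-normal, only time beyond 150 min compressed (by 35%) | 0.91 | 0.66 |
| Log-normal, only time beyond 180-220 min compressed | 0.93-0.94 | 0.40-0.53 |

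In the last row about half or more of the excess time has to disappear: 56% if compression starts at the median, 91% if it starts at about 220 min.

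**The case against.** **Loss of power.** A reader might infer that the rule halves the power of the primary comparison. The documents do not support that. A loss of that size needs the whole fall to come from a large compression of stays beyond about the median. Section 5.1.5 states a 10% fall in the mean and nothing about where it arises. For a uniform shift, a proportional fall or benefit in a random subset, Mann-Whitney is at most about 3 points less powerful and up to about 8 points more. The pathway (section 5.3) does not point to a tail-only effect either. The 30-minute progress checks depend on a coach being available and run throughout the stay, and other components reach most patients. This objection stands.

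**Certainty of the switch.** A reader might also infer that ED-LOS will certainly go to Mann-Whitney. Section 5.5 does not name ED-LOS there, section 5.1.5 assumes normality, and GEE might be meant as the primary model. This stands too: the switch is plausible, not prescribed.

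**Matter for an analysis plan.** Model details are commonly left to a statistical analysis plan, which is not shown here. That covers the link function and the handling of outliers. It does not cover a rule the protocol itself states, one branch of which does not address its own hypothesis.

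**GEE is not a free remedy.** Section 4 lists five hospitals and one optional. In a simulation with no effect, log-normal stays, an assumed within-hospital correlation of 0.03 and 300 per group, an uncorrected robust Wald test of the ratio of means rejected in about 15% of trials with five hospitals and 13% with six, against a nominal 5%. This stands, and it shapes the fix.

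**Conclusion.** The mismatch is real. The trial is framed and sized on mean ED-LOS, and the 466 reproduces exactly on that basis. Section 5.5 nevertheless lets an undefined judgement of normality replace the comparison of means with a rank test that has no estimate on the hypothesised scale and no allowance for hospital. It does not say which of three analyses decides.

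The effect on power runs from a gain of about 8 points to a loss of about half, according to an effect shape the protocol does not give. It should be reported as that range, not as a demonstrated loss. The power figures rest on assumed distributions, on the SD read as 77 min, and on independent patients. They ignore clustering and calendar time, so they compare the two tests and are not this trial's power. The case for a change rests on the conflict between hypothesis and test. It would hold even if no power were lost.

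**What to change.** State in section 5.5 that the single primary analysis of ED-LOS, whatever its distribution, is the planned GEE on the mean:

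- adjusted for hospital and calendar period, as the stepped-wedge design in section 1 requires;
- with a small-cluster correction to the standard errors, because there are only five or six hospitals;
- reporting a mean difference or a ratio of means with 95% CI, to be read against the 10% hypothesis.

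Keep medians, interquartile ranges and Mann-Whitney for ED-LOS as description only.

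The cost is a few sentences and no new data. There are two statistical downsides: means are more sensitive to a few extreme stays, for which the descriptive median gives context, and the corrected interval will be somewhat wider than an uncorrected one. Two practical points need checking. The software named in section 5.5 must be able to produce the correction. Period effects can be separated from the pathway only if hospitals start on different dates, whereas section 4 gives one planned start, January 2021.

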### **5.3.1 Control group**

Specialists in the hospitals with CTcue will be unaware of the patients functioning as controls during this study, since data for controls will be collected retrospectively. In the participating hospitals without access to CTcue, control patients will be gathered prospectively. The aim is that each participating hospital gathers a control group which will be compared with their intervention group.

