## 5.4 STUDY PARAMETERS / ENDPOINTS

### 5.4.1 Main study parameter/endpoint

#### *Baseline characteristics:*

- Age in years
- Gender (male/female)
- Referral category NSC
  - o Somatic
  - o Higher demand of care
  - o Cognitive problems
  - o Functional status
  - o Unexplained falls
- Main diagnosis at ED (DOT/DBC/ICD10)
- Way of arrival (per ambulance, public transportation, own transport, etc.)
- APOP-score
- Adherence to the recommended actions after APOP-screening and risk of functional decline
- Specialist seeing the patient and consulting specialists during ED-stay
- Diagnostic tests (X-ray, EKG, urinalysis, bladder scan and the frailty lab)
- ED-logistics (time of arrival at ED, duration of triage, triage colour, ED loss etc)
- In the case of admission: duration of admission (days) and reason for admission
- Living situation (independent, care at home, etc)
- Zip (postal code)
- Discharge destination (home, facility, care at home)
- Change in medication list after review
- Patient satisfaction

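### Section 5.5 does not say whether pooled tests or a hospital-clustered GEE decides ED-LOS, and with five or six hospitals a standard GEE without small-sample correction would not hold the 5% error rate

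*Protocol*

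**What the plan says.** Section 5.5 of the protocol first states that "Continuous variables will be analysed using independent t-tests", with Mann-Whitney tests for non-normal variables. Neither test contains hospital. Later in the same paragraph it says "Generalized Estimating Equations (GEEs) will be used, which adjust for observations made within the same hospitals being more alike". It attaches neither method to ED-LOS by name and gives no order between them. Every test is held to the same two-sided 5% level.

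Other sections bear on this:

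- The Summary calls the design a stepped-wedge cluster design. The order and number of steps are not given.
- Section 4 lists five hospitals and one optional hospital.
- Section 5.3.1 describes a within-hospital contrast: "The aim is that each participating hospital gathers a control group which will be compared with their intervention group".
- Section 5.1.5 adds that "A minimum number of control-patients will be established for each participating hospital". It gives no matching minimum for intervention patients.
- The sample size in section 5.1.5 is that of a simple two-group comparison of means, built on the hypothesis that "implementing the care pathway will reduce the mean ED-LOS with 10" percent. It has no allowance for clustering.

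**The concern.** ED-LOS is a primary objective. A pooled t-test and a hospital-clustered GEE can give different p-values and intervals on the same data. With no stated order, the deciding analysis could be chosen after the results are seen.

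Each candidate also has a weakness in this design. The pooled tests do not make the within-hospital comparison of section 5.3.1. They are exposed if the hospital mix differs between groups, or if a hospital's level shifts between its control and pathway periods. Section 4 itself expects COVID to change ED organisation during inclusion. The usual robust GEE variance is justified for many clusters; with five or six it is too small on average, and a normal reference distribution adds to the error. A chance difference in ED-LOS could then be declared an effect up to several times as often as the nominal 5%.

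**Working it through.** **Step 1. Reproduce the plan's sample size (section 5.1.5).** Inputs: difference 10% of 3 h 20 min = 20 min = 0.333 h; two-sided 5%; power 80%. The SD is printed as 1.17.

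n per group = 2 × (1.960 + 0.842)² × SD² / 0.333²

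- SD read as 1 h 17 min (1.283 h): 232.7, so 233 per group and 466 in total. This matches the protocol.
- SD read as 1.17 h: 194 per group, 388 in total. This does not match.

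The stated number is therefore that of an unclustered two-sample comparison, with the SD read as 1 h 17 min.

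**Step 2. Type I error of an uncorrected GEE, closed form.** Take K equal hospitals with equal before and after groups. The uncorrected robust Wald statistic equals the paired t on the K hospital differences times √(K/(K−1)). Hence:

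Type I error = 2 × P(t with K−1 df > 1.96 × √((K−1)/K))

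- K = 5: 1.96 × √(4/5) = 1.753, giving 15.4%.
- K = 6: 1.96 × √(5/6) = 1.789, giving 13.4%.

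No intracluster correlation (ICC) is needed. Using a t reference with K−1 df but no variance correction leaves 6.8% (K = 5) and 6.6% (K = 6). Adding the K/(K−1) variance correction gives exactly 5%. The interval must widen by 2.776 × √(5/4) / 1.96 = 1.58 with five hospitals.

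**Step 3. Simulation under no effect.** 600 patients (the target of 300 per group), 5 or 6 hospitals, 1,000 runs per setting, Monte Carlo standard error about 1 percentage point. The protocol gives no ICC, drift or step pattern. Assumed: ICC 0.01, 0.05 and 0.10; autocorrelation of hospital levels between periods 1.0 (stable) or 0.8 (drift).

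| Analysis and layout | Type I error |
|---|---|
| Uncorrected GEE, no period terms | 13-20% (K = 5); 11-16% (K = 6) |
| Uncorrected GEE, staggered, period terms fitted | 22-26% (K = 5); 19-24% (K = 6) |
| Pooled tests, before-after, stable hospitals | about 4-7% |
| Pooled tests, before-after, drift | 6-8% at ICC 0.01; 8-13% at 0.05; 13-23% at 0.10 |
| Pooled tests, staggered | 6-9% at ICC 0.01; 15-20% at 0.05; 25-32% at 0.10 |

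In the staggered layout with period terms, a t reference with K−1 df alone still leaves about 10-15%.

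**Step 4. Power once inference rests on hospitals.** Favourable case: balanced, stable hospital effects, SD 1.283 h, five hospitals, t with 4 df (critical value 2.776).

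- 233 per group: standard error = 1.283 × √(2/233) = 0.119 h; non-centrality = 0.333/0.119 = 2.80; power about 56%.
- 300 per group: standard error = 1.283 × √(2/300) = 0.105 h; non-centrality = 3.18; power about 67%.

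**The case against.** The protocol never says that its GEE is uncorrected. It names no variance estimator or reference distribution, and such detail commonly sits in a statistical analysis plan, which is not at hand. That stands: the 13-15% is conditional, not what the protocol prescribes.

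A reader might infer that the plan ignores hospital. It does not, because the paragraph that lists the pooled tests also names GEE for that purpose. Since neither method is tied to ED-LOS by name, the pooled tests may be generic tests for the many listed variables. The defect is a missing hierarchy more than a flat contradiction.

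A reader might also infer that the pooled tests are invalid. The figures do not support this in general: with stable hospital effects and similar splits they stay near 5%. The inflation rests on assumed ICC values together with drift or a staggered layout.

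Finally, the baseline list in section 5.4.1 includes items recorded after the pathway acts, such as discharge destination and satisfaction. One might read it as a proposed set of adjustment variables, but the protocol nowhere offers it as one. The loose label is minor.

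What remains is that the deciding analysis is not named, and that a GEE run in its standard form on this number of hospitals would miss the stated error rate.

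**Conclusion.** The point holds in this limited form. Section 5.5 leaves open which analysis decides ED-LOS, and neither candidate is safe as named.

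- **GEE.** The type I error is 15.4% with five hospitals and 13.4% with six. This assumes no small-sample correction and a balanced before-after layout; it does not depend on the ICC. With period terms in a staggered design the simulated figure is about 19-26%, which rests on the assumed step pattern, ICC and drift.
- **Pooled tests.** They are near nominal under stable hospital effects and similar splits. They reach about 15-20% in a staggered layout at an assumed ICC of 0.05, and there is little inflation at 0.01.

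If the statistical analysis plan already specifies a small-sample correction and names the primary model, the GEE part is answered. The protocol text would then only need to agree with it, and the power statement would still need revising.

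**What to change.** Name one primary ED-LOS analysis in section 5.5:

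- **Scale.** Use the mean, or a log-link model giving a ratio of means, to match the hypothesised reduction in the mean. Modelling log-transformed ED-LOS targets geometric means, which is a different quantity.
- **Terms.** Include pathway, hospital, calendar period, and pre-pathway covariates to be collected in both groups: age, sex, category of non-specific complaint and way of arrival. Do not adjust for items recorded after the pathway starts.
- **Inference.** Work at hospital level with a small-sample method. Examples are a mixed model with a random hospital-by-period term and Kenward-Roger or Satterthwaite degrees of freedom, or a t-based analysis of hospital-level differences. If a corrected sandwich is preferred, note that leverage-based corrections can be singular with hospital fixed effects. Changing only the reference distribution is not enough when period terms are fitted.
- **Other tests.** Keep t, Mann-Whitney and chi-square tests for descriptive tables.

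Confirm that SPSS 24.0, the only package named, can run the chosen method.

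**Cost.** No new data items are needed, but the change is not free. Intervals are about 1.58 times the naive GEE interval with five hospitals in the balanced case. The 80% power stated for 466 patients becomes about 56%, and about 67% at 600, under the favourable assumptions of step 4. Those figures include neither drift nor period terms. Section 5.1.5 should restate the power for the analysis actually chosen.

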## **6. ETHICAL CONSIDERATIONS**

### **6.1 Regulation statement**

The study will be conducted according to the principles of the Declaration of Helsinki (version 2004, May 22, 2007; [www.wma.net](http://www.wma.net)) in accordance with the Medical Research Involving Human Subjects Act (WMO).

### **6.2 Recruitment and consent**

Older adults presenting to their primary health care provider with a NSC will be considered for the care pathway. Every referring care professional will have a card, which provides information on how to refer a patient to the care pathway and to whom. Patients not referred by the GP can enter the care pathway if referred by the practitioner at a nursing home or if triage at the ED points to a NSC. If a patient meets all inclusion criteria, the primary health care provider will notify the specialist at the ED (internist, emergency physician or elderly care physician). If eligible and feasible, an ED-coach will introduce the patient to the care pathway and make sure the patient receives special care. Each participating hospital for the care pathway will sign a form to collect data for control patients beforehand.

### **6.3 Objection by minors or incapacitated subjects**

Minors will not be included in this study. For incapacitated subjects, the legal representative will be encountered for informed consent.

### **6.4 Benefits and risks assessment, group relatedness**

Participation in the care pathway is non-invasive. It includes specialized care for older adult patients presenting with NSCs at the emergency department. The burden regarding participation in this care pathway is comparable for capacitated adults and can be considered minimal.

### **6.5 Compensation for injury**

The sponsor/investigator has a liability insurance which is in accordance with article 7 of the WMO. Hospitals and caregivers / organisations other than hospitals have responsibilities and according insurance for the care of their patients.

## **7. ADMINISTRATIVE ASPECTS, MONITORING AND PUBLICATION**

### **7.1 Handling and storage of data and documents**

All data will be handled confidentially. Participant data will be safeguarded and coded by a subject identification code, therefore he or she will not be identifiable. Data will be handled according to the Dutch Personal Data Protection Act and stored in Research Manager. When it is necessary to be able to trace data for an individual subject, a subject identification code list can be used to link the data. The key to this list will only be given to the principal investigator. Only qualified research personnel will have access to confidential data. Research data will be stored for at least 15 years.

### **7.2 Amendments**

Amendments are changes made to the research after a favourable opinion by the accredited METC has been given. All amendments will be notified to the METC that gave a favourable opinion.

A 'substantial amendment' is defined as an amendment to the terms of the METC application, or to the protocol or any other supporting documentation, that is likely to affect to a significant degree:

- the safety or physical or mental integrity of the subjects of the study;
- the scientific value of the study;
- the conduct or management of the study;
- the quality or safety of any intervention used in the study.

All substantial amendments will be notified to the METC and to the competent authority.

Non-substantial amendments will not be notified to the accredited METC and the competent authority, but will be recorded and filed by the sponsor.

